## 10.4 Precautions Taken to Minimize Risks

As outlined above, the participants will be monitored closely during their participation in this study. The study vaccines have been produced according to cGMP. The vaccines will be administered by experienced investigators or study nurses with drugs and equipment for the treatment of anaphylaxis and other potential adverse reactions readily available. All vaccine doses will be given by IM injection to minimize injection site reactions such as pain.

## 10.5 Benefits

Volunteers will not receive any direct benefit from the vaccinations administered in this study. It is hoped that information gained in this study will contribute to the development of a safe and effective malaria vaccine.

## 10.6 Confidentiality

Participants will be informed (Appendix 5) that their data are held on file by Q-Pharm, that these data may be viewed by staff of Q-Pharm (including, where necessary, staff of Q-Pharm other than the named investigators), and that data may also be sighted by the sponsors’ monitor on behalf of the sponsor and by external auditors on behalf of either the sponsors or regulatory agencies.

All study-related information will be stored securely at the study site. All participant information will be stored in locked file cabinets in areas with access limited to study staff. All laboratory specimens, reports, study data collection, process and administrative forms will be identified by coded number only to maintain participant confidentiality. All computer entry will be done by coded number only, and all local databases will be secured with password-protected access systems. Forms, lists, logbooks, appointment books and any other listings that link participant ID numbers to other identifying information will be stored in a separate, locked file in an area with limited access.

The participants will similarly be informed that a report of the study will be submitted to the sponsors and may also be submitted to government agencies and perhaps for publication, but that they will only be identified in such reports by their study identification number and perhaps their gender and age.

## 10.7 Compensation

Volunteers who complete the study will be paid $1050 compensation for their participation in completing the study. The total payment will be divided over the course of the study with the final payment following the last visit.

Reserve participants who do not participate in the study will be paid $150 compensation for the inconvenience associated with their attendance for screening and for their attendance on the dosing day of vaccination, in case they are required to participate.

Participants who withdraw or are withdrawn from the study will be compensated on a fractional basis for their involvement unless they are withdrawn as a consequence of their misconduct and/or non-compliance.

## 10.8 Liability/Indemnity/Insurance

The study sponsor, QIMR, will ensure sufficient insurance is available to enable it to indemnify and hold the investigator(s) and relevant staff, including medical monitor as well as any hospital, institution, ethics committee or the like, harmless from any claims for damages for unexpected injuries, including death, that may be caused by the study drug but only to the extent that the claim is not caused by the fault or negligence of the participants or investigator(s). QIMR and PATH (a named party to the policy) agree to adhere to the guidelines of Medicines Australia for injury resulting from participation in a company sponsored trial, including the provision of “No-fault clinical trial insurance”.

Appendix 1 - MSP2 Schedule of Events

| **Procedures** | **WK** |  | **0** |  |  | **1** | **2** |  | **4** | **8** | **12** |  |  | **13** | **14** | **15** | **16** | **20** |
| --- | --- | --- | --- | --- | --- | --- | --- | --- | --- | --- | --- | --- | --- | --- | --- | --- | --- | --- |
|  | **Day** | **Screen** | **0** | **1** | **3** | **7** | **14** | **21** | **28** | **56** | **84** | **856** | **876** | **916** | **986** | **1056** | **1126** | **1406** |
| Obtain Informed Consent |  | X1 | X2 |  |  |  |  |  |  |  |  |  |  |  |  |  |  |  |
| Complete History and Physical |  | X |  |  |  |  |  |  |  |  |  |  |  |  |  |  |  |  |
| Clinical Evaluation |  |  | X |  | X | X | X |  | X | X | X |  | X | X | X |  | X | X |
| Distribute diary card |  |  | X |  |  | X | X |  |  |  | X7 |  |  | X | X |  |  |  |
| Phone call |  |  |  | X |  |  |  | X |  |  |  | X |  |  |  | X |  |  |
| Collect diary card |  |  |  |  |  | X | X |  | X |  |  |  |  | X | X |  | X |  |
| FBC & Diff, Biochem (9 mL)4 (14 ml) 5 |  | X | X5 |  | X |  | X5 |  |  | X | X5, 8 |  | X |  | X5 |  |  | X |
| Urinalysis |  | X |  |  |  |  |  |  |  |  |  |  |  |  |  |  |  |  |
| Pregnancy test3 (females) |  | X3 | X |  |  |  |  |  |  |  | X7 |  |  |  |  |  |  |  |
| HIV HCV, HBsAg  (10 mL) |  | X |  |  |  |  |  |  |  |  |  |  |  |  |  |  |  |  |
| **VACCINATION** |  |  | **X** |  |  |  |  |  |  |  | **X7** |  |  |  |  |  |  |  |
| Anti-MSP2 antibody ELISA  (10 mL) |  |  | X |  |  |  |  |  | X |  | X |  |  |  |  |  | X |  |
| Cell Mediated Immunity  (45 ml=40 mL [PBMC] + 5 ml [serum]) |  | X |  |  |  |  |  |  | X |  |  |  |  |  |  |  | X7 |  |
| Growth Inhibition Assay (GIA ) (from CMI plasma 2 mL for NIH assay) |  | X |  |  |  |  |  |  |  |  |  |  |  |  |  |  | X |  |
| Immunoflorescence Assay (IFA) with Ab (supernatent plasma off CMI whole blood) |  | X |  |  |  |  |  |  |  |  |  |  |  |  |  |  | X |  |
| Blood Volume (mL) |  | 64 | 19 |  | 9 |  | 14 |  | 55 | 9 | 19 |  | 9 |  | 14 | 9 | 55 | 9 |
| Cumulative Blood Volume (mL) |  | 64 | 83 |  | 92 |  | 106 |  | 160 | 169 | 189 |  | 193 |  | 212 | 221 | 276 | 285 |

**1 *Screening Consent,* 2*Particpation Consent,* 3 *Screening pregnancy (female only) = Serum Β-HCG (+10 mL blood) , 4Biochemistry to include: creatinine, AST and ALT,5 with CPK, 6 Visit Not required for Participant withdrawn from further Vaccination 7 Procedure not required for Participant withdrawn from further Vaccination; 8 CPK not required if Participant withdrawn from further Vaccination***

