# 3.0 Study Design

## 3.1 Overall Design

The study is a Phase 1 dose-escalating clinical trial in healthy adult malaria-naïve volunteers designed to evaluate the safety and immunogenicity of the MSP2-C1/ ISA720 malaria vaccine.

Volunteers will be recruited, and after providing written informed consent, will undergo eligibility screening, including medical history, physical examination, laboratory investigations including haematology testing, liver and renal function tests, pregnancy (females only), HIV, Hepatitis B and C screening and urinalysis. Those determined to be eligible, based on the inclusion and exclusion criteria described in **Section 4** in this protocol will be enrolled and randomised into the study. Participants will receive one of two dose regimens of the MSP2-C1/ISA720 vaccine or ISA720 as a control. Serum pregnancy tests will be performed on female volunteers of child bearing potential prior to enrollment and urine pregnancy testing prior to each vaccination; these females will be counselled to avoid becoming pregnant during the study. Clinically significant abnormalities will be reviewed by the investigators and referral for follow-up care will be provided as indicated. For eligible participants, the Day 0 visit will be scheduled for receipt of the first vaccination. Vaccinated volunteers will be observed for immediate reactions following each vaccination for 30 minutes. Volunteers will return to the clinic on Days 3, 7, 14 and 28 following each vaccination for clinical assessment, and will be given diary cards to record and grade local and systemic signs and symptoms. Phone contact will be made on D1 & D21 following each vaccination. Volunteers will also return 56 days following vaccinations 1 and 2 for screening prior to each subsequent vaccination. See **Appendix 1 Schedule of Assessments, and Table 1** for a tabular description of the vaccination schedule.

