Thirty volunteers will be enrolled and assigned to one of two dose groups (10 or 40µg) or ISA720 Control as outlined in **Table 1**. All vaccines and the ISA720 Control will contain the same amount of Montanide® ISA720. As with other recombinant protein vaccines, hypersensitivity reactions would be expected to occur within the first 24 hours after receipt of the vaccine, and other severe local or systemic reactions within 72 hours. As outlined above, delayed local reactions have been observed in previous ISA720 vaccine studies. Thus, volunteers will be reviewed on days 3, 7, 14 and 28 following each vaccination, and vaccinations will be staggered within the higher dose cohort such that 5 volunteers will be vaccinated 4 weeks prior to the remaining 10 volunteers. Stopping rules as detailed in **Section 7.5** below will be in place to enable suspending the trial until review by the safety monitoring committee (SMC).

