### 6.4.1 Clinical Monitoring and Evaluation of Subjects Withdrawn from Vaccinations

Participants may be withdrawn from further vaccinations as described in Sections 4.4, 4.5 and 4.6 above. Participants who have received at least one vaccination will be encouraged to continue in the study for safety follow-up according to a modified visit schedule.

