### 6.4.1.1 Modified Visit Schedule for Participants Withdrawn after First Vaccination

All visits from Screening to Study Day 56 +/- 7 (2 months after FIRST vaccination, visit 6) as above.

Study Day 84 +/- 7 (Visit 7)

1. Medical Investigator to perform medical history and physical examination.

2. Obtain approximately 24 mL of blood for haematology, (FBC and differential), biochemistry (creatinine, liver function tests), and humoral immunity studies by anti-MSP2 ELISA.

3. Record vital signs.

4. Record adverse events and concomitant medications.

Study Day 168 +/- 7 (Visit 13)

1. Medical Investigator to perform medical history and physical examination.

2. Obtain approximately 24 mL of blood for haematology, (FBC and differential), biochemistry (creatinine, liver function tests), and humoral immunity studies by anti-MSP2 ELISA.

3. Record vital signs.

4. Record adverse events and concomitant medications.

Study Day 336 +/- 14 (Visit 18)

1. Medical Investigator to perform medical history and physical examination including examination of injection site, emphasising examination of any acute complaints.
2. Record vital signs.
3. Obtain 55 ml of blood for collection of blood for humoral immunity studies by anti MSP2 ELISA, GIA and IFA, and PBMC and serum for study of cell mediated immunity.

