### 6.4.1.2 Modified Visit Schedule for Participants Withdrawn after Second Vaccination

Study Day 168 +/- 7 (Visit 13)

1. Medical Investigator to perform medical history and physical examination.

2. Obtain approximately 24 mL of blood for haematology, (FBC and differential), biochemistry (creatinine, liver function tests), and humoral immunity studies by anti-MSP2 ELISA.

3. Record vital signs.

4. Record adverse events and concomitant medications.

Study Day 336 +/- 14 (Visit 18)

1. Medical Investigator to perform medical history and physical examination including examination of injection site, emphasising examination of any acute complaints.
2. Record vital signs.
3. Obtain 55 ml of blood for collection of blood for humoral immunity studies by anti MSP2 ELISA, GIA and IFA, and PBMC and serum for study of cell mediated immunity.

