## 7.2 Assessment of Adverse Events

### 7.2.1 Identification of AEs

Assessment of safety will include clinical observation and monitoring of hematological, chemical and immunologic parameters. Safety will be evaluated by monitoring of volunteers for local and systemic adverse reactions during the course of the trial. Volunteers will be closely observed in the clinic for approximately 30 minutes after each vaccination and contacted by telephone on Day 1 and 21 after each vaccination to inquire about reactions. Additionally, volunteers will return to the clinic on Days 3, 7, 14 and 28 following each vaccination for clinical assessments. Clinical staff must accurately measure the total affected area of any volunteer presenting with erthyema, swelling and induration with a ruler or tape measure. Measurement must be documented at each visit until resolution. Clinical staff may elect to photograph injection site reactions over time for any volunteer. Clinical staff must apply the Brighton’s Collaboration Assessment Tool on any nodules or suspected nodules or to differentiate induration from a nodule.

For 13 days after each immunisation, volunteers will be asked to keep daily diaries of symptoms, recording oral temperature, as well as a subjective assessment of the extent of induration, erythema, pain/ tenderness at the site of injection, and any systemic signs and symptoms. The size of any injection-site reaction will be measured using a standardized clear plastic measurement device and recorded in the volunteer symptom diary. A third diary card will be given at the 14 day visit following each vaccination for the volunteer to record only injection site reactions. (Days 14-28).

At each clinic visit to Day 28, clinic staff will review the volunteer diaries, confirm the symptoms experienced and record AEs as appropriate in the source document. Individual symptom reports of pain, tenderness and muscle ache at injection site will be recorded as the AE term of pain at injection site.

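### Read literally, Appendix 1 footnote 6 waives the remaining post-dose-2 safety contacts for a volunteer withdrawn between doses 2 and 3, and Section 6.4.1.2 has no line that keeps them

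*Protocol*

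**What the plan says.** **General rule.** Section 3.1 states: "Volunteers will return to the clinic on Days 3, 7, 14 and 28 following each vaccination for clinical assessment". It gives delayed local reactions seen with ISA720 as the reason: "Thus, volunteers will be reviewed on days 3, 7, 14 and 28 following each vaccination". Section 7.2.1 repeats the visits for adverse event identification ("volunteers will return to the clinic on Days 3, 7, 14 and 28 following each vaccination for clinical assessments") and adds calls: volunteers are "contacted by telephone on Day 1 and 21 after each vaccination to inquire about reactions".

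**Withdrawn volunteers.** Section 6.4.1 says that those who have had at least one dose are "encouraged to continue in the study for safety follow-up according to a modified visit schedule". Two schedules follow.

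- Section 6.4.1.1 (withdrawn after dose 1) opens with "All visits from Screening to Study Day 56 +/- 7 (2 months after FIRST vaccination, visit 6) as above" and then lists Days 84, 168 and 336.
- Section 6.4.1.2, headed "Modified Visit Schedule for Participants Withdrawn after Second Vaccination", has no such opening line. It lists Days 168 and 336 only.

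**Schedule table.** In Appendix 1, superscript 6 sits on Days 85, 87, 91, 98, 105, 112 and 140, and on the second page on Days 169 to 196. Footnote 6 reads "Visit Not required for Participant withdrawn from further Vaccination". Footnote 7 waives single procedures after withdrawal, including CMI at Day 112. Footnote 8 waives CPK at Days 84 and 168 after withdrawal.

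**The concern.** Footnote 6 draws no line between a volunteer who never received dose 2 and one who received it and was then stopped. For the first, waiving Days 85 to 140 makes sense. For the second, those days are the safety follow-up of a dose already given, and 6.4.1.2 does not restore them. A site working from the table and the modified schedule would find Day 168 to be the next contact.

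Safety and tolerability is the primary objective. Section 2.3.3 places delayed local reactions 10 to 28 days after vaccination, which is the period the repeated reviews are there to cover. Some volunteers stopped in this interval would be stopped because of a reaction to dose 2. Any missing follow-up would then be related to the safety outcome, in arms of only 12 active volunteers each.

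**Working it through.** The protocol states no figure on this point to reproduce. The check sets the texts side by side and counts days.

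**Can withdrawal fall between Day 84 and Day 168?** Yes.

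- Section 7.5.1 B withdraws a volunteer for certain Grade 3 systemic events that begin within two days of a dose.
- Section 7.5.1 C does so for laboratory events, and bloods are drawn on Day 87.
- Section 4.3 is checked at every visit.
- Most of Section 4.6 can apply at any time.
- Section 6.4 reassesses continued eligibility at Days 91 and 140.

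**Inputs.** Dose 2 is Day 84. The next visit in 6.4.1.2 is Day 168 ± 7, that is Days 161 to 175. The delayed-reaction window for dose 2 runs from 84 + 10 = 94 to 84 + 28 = 112. Three scheduled contacts fall in it: Days 98, 105 and 112. CPK is scheduled on Days 0, 14, 84 (before the dose), 98, 168 (before the dose, waived after withdrawal) and 182.

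**Count.** The gap is 168 minus the day of withdrawal. Its range uses 161 and 175 in place of 168. Nominal visit days are used.

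| Withdrawn at | Contacts that could be omitted | Gap in days (range) | Required visits or calls left in Days 94–112 | Day 98 CPK |
|---|---|---|---|---|
| Day 87 | 91, 98, 105, 112, 140 (5) | 168 − 87 = 81 (74–88) | 0 of 3 | could be missed |
| Day 91 | 98, 105, 112, 140 (4) | 77 (70–84) | 0 of 3 | could be missed |
| Day 98 | 105, 112, 140 (3) | 70 (63–77) | 1 of 3 | already drawn |
| Day 112 | 140 (1) | 56 (49–63) | 3 of 3 | already drawn |

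The ceiling is withdrawal on Day 84 after the injection: all seven contacts (five clinic visits, two calls) and a gap of 84 days. A volunteer withdrawn before Day 98 has no required CPK at any time after dose 2.

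**Comparison inside the protocol.** Section 6.4.1.1 keeps 56 days of visits after dose 1. The same span after dose 2 ends at 84 + 56 = Day 140, which is the last day carrying footnote 6 on that page. Section 7.5.2, for a stopped cohort, follows volunteers until their events resolve or for at least 30 days after the last dose. No such minimum is stated for one volunteer withdrawn after dose 2.

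**The case against.** **The intent can be guessed.** This largely stands. Section 6.5 withholds diary cards only when no vaccination is given. On Days 169 to 196 footnote 6 can only mean that dose 3 was not given, since no further dose remains to be withdrawn from. Footnote 7 on the Day 112 CMI cell would be redundant if the whole visit were always waived, though the same pairing appears at Day 196, so that clue is weak. The likely meaning is that Days 85 to 140 are waived only if dose 2 was not given. No section says so.

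**The scope is narrow.** This stands too. Section 6.4.1 refers to Sections 4.4, 4.5 and 4.6. Section 4.4 is checked before each immunisation and 4.5 at the time of a scheduled one, so after dose 2 both normally fall at Day 168, when Days 85 to 140 are past. This may explain why 6.4.1.2 starts there. Only mid-interval withdrawals, for example under 4.3, 4.6 or 7.5.1, are exposed.

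**A special rule may depart from a general one.** It may, and 6.4.1 provides for a modified schedule. But 6.4.1.1 shows that such a schedule was meant to keep the follow-up of the dose given, and 6.4.1.2 is silent on those visits without expressly waiving them.

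**Other safeguards exist.** Known events are followed to resolution, a clinician can be reached at all hours, and 6.4.2 allows extra visits with CPK. A Grade 3 clinical event probably or definitely related to vaccine generally also triggers the hold in Section 7.5. So the volunteer stopped for such an event is the best protected. None of these schedules the detection of a new event.

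**Stronger readings that do not hold.**

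- A reader might infer that Sections 4.3 and 4.4 are contradicted as well. They only encourage such volunteers to stay in the safety evaluation and fix no visits.
- A reader might infer that the delayed-reaction window goes wholly unobserved. The later cards are handed out at Days 91 and 98, but nothing says that diaries stop once a dose has been given. The claim covers clinic visits and calls only.
- A reader might multiply the 11% in Section 2.3.3 by an assumed number of withdrawals. That figure is an average over other vaccines, is described as tending to rise with dose and repeat injections, and counts reactions that occur, not reactions missed.

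**Conclusion.** The point holds as a drafting gap with a practical consequence. The table's literal wording and the missing line in 6.4.1.2 together let a site omit post-dose-2 contacts that 3.1 and 7.2.1 require after each vaccination.

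The size depends on the day of withdrawal. It is largest for the earliest withdrawals and is down to the Day 140 visit alone for withdrawal at Day 112. The counts assume that the site applies footnote 6 literally and arranges no unscheduled visit. The protocol gives no expected number of mid-interval withdrawals, so no total is estimated; it is likely to be small.

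A reader might conclude that the protocol deliberately gives up safety follow-up after dose 2. The documents do not support that. The evidence points to an omission, worth correcting because it touches the primary objective and the correction is simple.

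**What to change.** Make three small edits.

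1. Open Section 6.4.1.2 with a line such as: *Clinical and safety assessments (clinic visits, phone calls, diary cards and safety bloods, including the Day 98 CPK) continue unchanged from Screening to visit 12 (Day 140 ± 7). CMI sampling at Day 112, and the GIA and IFA taken from it, is not required after withdrawal.*
2. Limit footnote 6 on Days 85 to 140 to participants who did not receive the second vaccination. Its use on Days 169 to 196 can stay.
3. Extend footnote 7 to the Day 112 GIA and IFA cells so that they match the CMI cell, because both assays use that sample.

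Simply copying the opening line of 6.4.1.1 would not do. It would bring back the Day 112 PBMC draw that footnote 7 already waives. The Day 112 ELISA cell carries no waiver, so the sponsor should say whether that sample is still wanted.

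The cost is a wording amendment. No visit is added beyond those already planned for every recipient of dose 2.

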Appendix 1 - MSP2 Schedule of Events

| **Procedures** | **WK** | **24** |  |  | **25** | **26** |  | **28** | **48** |
| --- | --- | --- | --- | --- | --- | --- | --- | --- | --- |
|  | **Day** | **168** | **1696** | **1716** | **1756** | **1826** | **1896** | **1966** | **336** |
| Clinical Evaluation |  | X |  | X | X | X |  | X | X |
| Distribute Diary Card |  | X**7** |  |  | X | X |  |  |  |
| Phone Call |  |  | X |  |  |  | X |  |  |
| Collect Diary Card |  |  |  |  | X | X |  | X |  |
| FBC & Diff, Biochem (9 mL)4 (14)5 |  | X5, 8 |  | X |  | X5 |  |  |  |
| Urine pregnancy test (females)3 |  | X7 |  |  |  |  |  |  |  |
| **VACCINATION** |  | **X7** |  |  |  |  |  |  |  |
| Anti-MSP2 antibody ELISA (10 mL) |  | X |  |  |  |  |  | X | X |
| Cell Mediated Immunity (45 ml=40 mL [PBMC] + 5 ml [serum]) |  |  |  |  |  |  |  | X**7** | X |
| Growth Inhibition Assay (GIA ) (from CMI plasma 2 mL for NIH assay) |  |  |  |  |  |  |  | X | X |
| Immunoflorescence Assay (IFA) with Ab (supernatent plasma off CMI whole blood) |  |  |  |  |  |  |  | X | X |
| Blood Volume (mL) |  | 19 |  | 9 |  | 14 |  | 55 | 55 |
| Cumulative Blood Volume (mL) | 285 | 304 |  | 313 |  | 327 |  | 382 | 442 |

**1 *Screening Consent,* 2*Particpation Consent,* 3 *Screening pregnancy (female only) = Serum Β-HCG (+10 mL blood) , 4Biochemistry to include: creatinine, AST and ALT,5 with CPK, 6 Visit Not required for Participant withdrawn from further Vaccination. 7 Procedure not required for Participant withdrawn from further Vaccination; 8 CPK not required if Participant withdrawn from further Vaccination***

